**Discussion:**

The current study addresses barriers to screening in this population by providing educational and motivational information for both survivors and physicians regarding the value of periodic skin examinations. It also utilizes innovative mobile health technology to encourage and motivate (that is activate) survivors to conduct skin self-examinations, request physician exams, and obtain treatment when worrisome lesions are found. Finally, as a comparative effectiveness trial, this study isolates the effects of adding specific components to the patient activation intervention to test the most effective intervention for enhancing skin examination vigilance among this high-risk group.

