### Power calculations

Sample size considerations are based on an equal allocation of participants to intervention arms. Our primary outcome focuses on increases in both physician screening and skin self-examination; the prevalence of screening and expected effect sizes are derived from rates of physician screening in the CCSS population [32,56]. Similar increases for self-screening were found in a trial focused on skin self-examination amongst the siblings of melanoma patients conducted by Geller and Emmons [50]. Assuming that baseline physician screening rates are 30% across all randomization groups, a 10 to 15% increase in physician screening rates would be considered a clinically significant improvement. Based on an estimated 25% attrition rate by month 18, we propose recruiting 801 subjects who will be evenly divided across the 3 intervention groups. Using a main effects model, the design has at least 80% power to detect a 15% difference across any of the arms even if one takes a conservative 0.025 threshold for statistical significance. This is based on a 2-degree of freedom chi-squared test with n = 200 in each arm, assuming the screening rate in the PAE arm is 30% and at least one of the other arms is 15% higher. The actual power in this scenario is 85%. We will use a conservative 0.025 threshold to account for multiple comparisons.

In the unexpected case that the PAE-alone arm is found to be superior to the other 2 arms, we will have a number of mechanisms in place to study this from our baseline, 12- and 18-month surveys. In particular, we will be asking many questions on physician screening of the participants in all three conditions. It could be that participants are deterred by added involvement of their physicians, although the literature shows that physician prompts are some of the greatest influences in increasing screening behaviors. We will also have a series of questions specific to Arm 3 participants to test if there has been any part of the addition of the technology component that was off-putting (for example, some participants who are either overwhelmed, do not understand how to utilize it, or perhaps do not trust the transmission of their personal health information).

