There are many strengths to the current study, particularly regarding the use of innovative technology and methods. First, we are targeting the three primary factors needed to result in reduced risk of serious skin cancers: (1) patient skin self-examinations; (2) physician full-body skin exams; and (3) rapid access to dermatologist evaluation of worrisome lesions. Second, we are focusing on both patient activation, a very important but not previously studied component of increasing skin cancer early detection, as well as activating patients’ primary physicians to conduct skin exams while providing them with the educational information needed to do so effectively. Third, we are providing a subset of study participants with a dermatoscope that easily attaches to a variety of smartphones or tablets to provide high-quality photographs of suspect lesions that will maximize the quality of teledermoscopy and increase access to evaluation. Because this technology is rapidly evolving, it is likely that the cost of such devices will continue to decrease and become increasingly available to the general population. Finally, this study has been designed as a comparative effectiveness trial, which will isolate the effects of adding specific components to the patient activation intervention. The inclusion of an economic component is just one reason to call this study a comparative-effectiveness trial. We strongly considered employing a true control group that would receive no website education or text messages. Upon much reflection though, it was felt that the inclusion of such activities could be at once effective, easy to implement, and have a broad reach.

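### The claim of at least 80% power for a 15-point difference holds only if the third arm lies near one of the extremes, and it is not the power of the added-component comparisons

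*Protocol article*

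**What the plan says.** The three arms are nested (Design overview and Table 1): PAE; PAE plus physician activation (PAE + MD); and PAE + MD plus teledermoscopy (PAE + MD + TD). Aim 1 concerns PAE with and without these additions. The abstract's discussion says "this study isolates the effects of adding specific components to the patient activation intervention", and the main Discussion lists the same thing as a strength of the design: "which will isolate the effects of adding specific components to the patient activation intervention".

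The Power calculations section recruits 801 participants in three equal groups, allows 25% attrition by month 18, and treats a 10 to 15% increase in physician screening as clinically significant. It then states that "the design has at least 80% power to detect a 15% difference across any of the arms", even at a 0.025 threshold. On the basis for this it says: "This is based on a 2-degree of freedom chi-squared test with n = 200 in each arm". The rates under the alternative are PAE at 30% and one or more of the remaining arms 15 points above it, with no rate given for the third arm. It continues: "The actual power in this scenario is 85" per cent. The paragraph closes with "We will use a conservative 0.025 threshold to account for multiple comparisons", without naming the comparisons. The article gives no power for any pair of arms.

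**The concern.** Two features of the power statement go further than its basis allows.

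First, the stated scenario fixes two arms (30% and 45%) and leaves the third open. The power of a 2-df test depends on all three rates, so a minimum has to hold for the least favourable position of the third arm. That position is near the middle, which is where the arms would fall if each added component contributed part of the gain.

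Second, a 2-df test asks whether the arms differ at all. The stated purpose asks what physician activation adds to PAE and what teledermoscopy adds to PAE + MD. Those are two 1-df contrasts, and their power is a different number. Someone who takes 85%, or at least 80%, as the chance of showing that a component works will be too optimistic. The gap is largest at the 10-point increase that the article itself calls clinically significant.

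**Working it through.** **Inputs (Power calculations section).** 801 × 0.75 = 600.75, so n = 200 per arm. Alpha = 0.025. PAE = 30%, at least one other arm = 45%. I read "15% higher" as 15 percentage points, because that reading reproduces the 85%.

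**Global test.** Noncentrality λ = n Σ(pᵢ − p̄)² / [p̄(1 − p̄)]. Power is the probability that a noncentral chi-squared variable (2 df, λ) exceeds 7.378, the 97.5th percentile of chi-squared with 2 df.

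*The article's figure first.*
- 30/30/45%: p̄ = 0.35, sum of squares 0.0150, λ = 200 × 0.0150 / 0.2275 = 13.19, power 85.9%.
- 30/45/45%: p̄ = 0.40, sum of squares 0.0150, λ = 200 × 0.0150 / 0.24 = 12.50, power 83.7%.

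Simulation gives 85.5% and 84.8%. The stated 85% is right for these two configurations.

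*Third arm between the extremes.*

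| Rates (%) | p̄ | Sum of squares | λ | Power |
|---|---|---|---|---|
| 30/35/45 | 0.3667 | 0.01167 | 10.05 | 73.5% |
| 30/37.5/45 | 0.3750 | 0.01125 | 9.60 | 71.2% |
| 30/40/45 | 0.3833 | 0.01167 | 9.87 | 72.6% |

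Simulation gives 71.4% for 30/37.5/45%. Moving the third arm in small steps from 30% to 45% gives a minimum of 71.1% near 38%. Power is 80.3% with the third arm at 32% and has fallen to 79.6% at 32.25%. At the other end it is 79.7% at 43.5% and 80.4% at 43.75%. So 80% needs the third arm within about 2 points of 30% or about 1.5 points of 45%. If the third arm lies outside 30 to 45%, the spread is wider than 15 points and power is higher.

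**Adjacent contrasts.** Two-sided 0.025, z = 2.241, pooled variance under the null: power = Φ[(|p₂ − p₁| − z·s₀)/s₁], with s₀ = √[2p̄(1 − p̄)/n] and s₁ = √[(p₁(1 − p₁) + p₂(1 − p₂))/n]. For 30 vs 45%: s₀ = 0.0484, s₁ = 0.0478, (0.15 − 0.1085)/0.0478 = 0.867, power 80.7%. In the same way:

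| Contrast (%) | Step | Power at 200 per arm |
|---|---|---|
| 30 vs 45 | 15 | 80.7% |
| 45 vs 60 | 15 | 78.0% |
| 30 vs 40 | 10 | 44.2% |
| 40 vs 50 | 10 | 40.8% |
| 30 vs 37.5 | 7.5 | 25.5% |
| 37.5 vs 45 | 7.5 | 23.6% |

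**How often a significant global test leaves the component question open.** Simulated share of significant global tests in which neither adjacent contrast reaches 0.025:
- 30/30/45% or 30/45/45%: about 8% (for the first, 0.0677/0.8554).
- 30/45/60%: under 1%.
- 30/40/50%: about 21%, with global power near 94%.
- 30/37.5/45%: 36% (0.2587/0.7139).

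**The case against.** A reader might infer that the 2-df test is the trial's only or primary analysis, that the trial therefore cannot attribute an effect to a component, and that the test should be replaced by two Bonferroni-adjusted contrasts. The document does not support this.

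- The section gives the 2-df test as the basis of a power figure and nowhere calls it the primary or sole analysis. The full protocol and analysis plan are not shown and may define arm comparisons.
- The 0.025 threshold for multiple comparisons, and the discussion of PAE alone proving superior to the other arms, suggest that arm-level comparisons are intended.
- With three arms, pairwise tests carried out only after a significant global test at the same level control the familywise error for that outcome.
- The design does isolate each component, since adjacent arms differ by one element. The sentences that say so make no power claim.
- In the two configurations that reproduce the 85%, only about 8% of significant global tests lack a significant adjacent contrast. The 36% comes from 7.5-point steps, below the range the article calls clinically significant.
- Using only the two adjacent contrasts would drop Arm 3 vs Arm 1, which has about 81% power at 30 vs 45%. Replacing the global test is therefore a trade-off.

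All of this stands, and it removes the case for replacing the test. It does not rescue the power statement. The shortfall to about 71% arises under the section's own assumption and for its own test. No later analysis plan changes the power that 200 per arm gives the component contrasts.

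**Conclusion.** The power claim is wrong as written. The 85% is correct for the global test when the third arm equals one of the two extremes. As a minimum for a 15-point difference, 80% is not delivered: power is about 71 to 73% in the intermediate configurations tried. For the comparisons that answer the component question, power at 0.025 is about 78 to 81% for a 15-point step, 41 to 44% for a 10-point step and 24 to 26% for a 7.5-point step.

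These figures assume 200 evaluable participants per arm, percentage-point differences, unadjusted comparisons of proportions, and 0.025 available in full to each contrast. The article does not say which comparisons the 0.025 covers. If it had to be split again between the two contrasts (0.0125 each), 30 vs 45% would have about 73%.

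The choice of a global test is not itself an error, and the trial is not shown to be unable to attribute effects.

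**What to change.** In the Power calculations section:

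1. State that 84 to 86% is the power of the 2-df test at 0.025 with 200 per arm when the third arm is at 30% or 45%. Give about 71% as the minimum when the three rates span 15 points.
2. Name PAE + MD vs PAE and PAE + MD + TD vs PAE + MD as the comparisons that answer the component question, and say what the 0.025 covers. One valid route is to test them at 0.025 only after a significant global test at 0.025.
3. Report their power: about 81% for 30 vs 45%, 78% for 45 vs 60%, 41 to 44% for 10-point steps and 24 to 26% for 7.5-point steps. If the global test comes first, give the joint probability instead. In simulation the 30 vs 45% step then has about 78% (30/30/45%) or 77% (30/45/45%).

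This is a change of wording. The global test stays, and no participants, visits or data are added. The cost is a less favourable stated power, and an open acknowledgement that a 10-point effect of a single component would more likely than not be missed.

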## Discussion

Focus on the long-term health outcomes of survivors of childhood cancer is of vital public health significance, as their 5-year survival rates now exceed 80%. Survivors treated with radiation therapy are currently at increased risk of developing both melanoma and basal cell carcinoma; incidence of squamous cell carcinoma may also emerge as the population ages. In theory, early detection can save lives and reduce morbidity, in practice though, screening rates are sub-optimal [32,56]. Less than optimal screening rates may be driven by lack of awareness of risk and lack of knowledge of how to conduct skin examinations by patients and physicians alike. The ASK study will address many of these barriers by providing educational and motivational information for both survivors and physicians regarding skin examinations, prompts via text messaging for survivors, and print and online resources for patients and providers. Equally important, we will attempt to narrow the interval from first detection of suspected skin cancer to treatment through the added dimension of teledermoscopy, which provides highly accurate preliminary information about the morphology of a lesion and can, in turn, lead to expedited care if needed.

There are a number of potential limitations, including recall bias and social desirability bias, specific to one of the three study conditions. Although it is highly unlikely that PAE alone or PAE with added interventions would cause worse outcomes than standard-of-care, because there is not a control group with no PAE, the study will not be able to detect such potential outcomes. In addition, social desirability may incline some participants to answer questions in a way that they think will be considered favorable by others. For example, if participants see that study researchers promote monthly skin self-checks, some may over report this behavior to appear more compliant with the expectations and desires of the researchers. Potentially over reporting positive behavior and/or under reporting negative behavior could bias the data and lead to inaccurate conclusions. However, consideration was given to ensure that questions and response options were not phrased in a way that would incline participants to choose a response because they felt it was ‘correct’. Another possible limitation is that the study staff will not observe participant performance of skin self-examination; therefore, the accuracy of these exams will not be able to be validated. The same is true regarding the accuracy and thoroughness of physician skin exam reports although documentation of screening will be verified through chart review. However, we have provided numerous resources to instruct and guide both participants and physicians regarding how to perform thorough, accurate skin examinations in several mediums (for example, written instructions, step-by-step guides with illustrations, and video tutorials). An additional potential limitation is that physicians may perform clinical skin examinations but may not document them in their patients’ charts, resulting in underreporting of clinical skin exams.

There are many strengths to the current study, particularly regarding the use of innovative technology and methods. First, we are targeting the three primary factors needed to result in reduced risk of serious skin cancers: (1) patient skin self-examinations; (2) physician full-body skin exams; and (3) rapid access to dermatologist evaluation of worrisome lesions. Second, we are focusing on both patient activation, a very important but not previously studied component of increasing skin cancer early detection, as well as activating patients’ primary physicians to conduct skin exams while providing them with the educational information needed to do so effectively. Third, we are providing a subset of study participants with a dermatoscope that easily attaches to a variety of smartphones or tablets to provide high-quality photographs of suspect lesions that will maximize the quality of teledermoscopy and increase access to evaluation. Because this technology is rapidly evolving, it is likely that the cost of such devices will continue to decrease and become increasingly available to the general population. Finally, this study has been designed as a comparative effectiveness trial, which will isolate the effects of adding specific components to the patient activation intervention. The inclusion of an economic component is just one reason to call this study a comparative-effectiveness trial. We strongly considered employing a true control group that would receive no website education or text messages. Upon much reflection though, it was felt that the inclusion of such activities could be at once effective, easy to implement, and have a broad reach.

Having such information from patients in the PAE group aligns with basic principles of comparative effectiveness research that is ‘designed to inform health care decisions to prevent, diagnose and treat health conditions by providing evidence of the effectiveness, benefits, and harms of various treatment options generated from research studies comparing multiple ways to deliver health care’ [57,58], all key features of the current study. In addition, this study intends to translate and disseminate research findings to diverse stakeholders at its conclusion to inform patients, providers, and decision-makers about which interventions are most effective for patients under specific circumstances, another key feature of comparative effectiveness trials [57]. This study represents the first attempt that we are aware of to employ disseminable and scalable technologies to activate high-risk patients to examine their skin for cancer, seek physician exams, and obtain expedited treatment.

It is anticipated that results from this intervention will have important implications for childhood cancer survivors and other high-risk populations, including organ transplant recipients (>225,000 recipients) and first-degree relatives of melanoma patients (>2 million Americans), all of whom share strong deficits in skin self-examinations and receipt of physician examinations for skin cancer [50,59-62].

## Trial status

We have not completed patient recruitment at the time of submission.

## Abbreviations

ABCDE: Asymmetry, Border, Color, Diameter, Evolution
ASK: Advancing Survivors’ Knowledge
BCC: basal cell carcinoma
CCSS: Childhood Cancer Survivor Study
ED: Early Detection
HCP: Health Care Provider
HIPAA: Health Insurance Portability and Accountability Act
FU5: Childhood Cancer Survivor Study Follow-Up 5 survey
LED: light-emitting diode
PAE: Patient Activation and Education
PAE + MD: Patient Activation and Education plus physician activation
PAE + MD + TD: Patient Activation and Education plus physician activation, plus teledermoscopy
PAM: Patient Activation Measure
RBRVS: Resource Based Relative Value Scale
TSSE: thorough skin self-examination
US: United States
